### Safety monitoring and harms

Doll therapy is considered a low-risk psychosocial intervention, but potential adverse responses include distress, agitation, possessiveness, interpersonal conflict, family concern, worsening confusion, or over-attachment to the doll. Each participant in the intervention arm will be assigned an individual doll, and dolls will not be shared between residents. Dolls will be cleaned according to each facility’s infection-control procedures while preserving participants’ sense of ownership and comfort.

Resident assent will be monitored throughout the study. Refusal or dissent may be verbal, such as saying no or asking staff to remove the doll, or non-verbal, such as pushing the doll away, turning away repeatedly, crying, showing fear, increased agitation, or clear discomfort. If a resident shows refusal or distress, staff will stop the interaction for that occasion, remove or set aside the doll respectfully, provide reassurance, and record the event. Reintroduction may be attempted only when the resident is calm and willing. Two consecutive sessions with refusal or significant distress will trigger an individualized review by the site clinician; three consecutive refusals or any persistent doll-related distress will result in discontinuation of doll exposure for that participant, with the resident retained in the intention-to-treat analysis.

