Adverse events will be graded as mild (transient distress resolving within the session), moderate (distress persisting beyond the session but resolving within 24 h, or non-injurious behavioral escalation), or severe (sustained distress beyond 48 h, hospitalization, injury, suspected harm to self or others, or death). All adverse events will be documented within 24 h by the site coordinator and reviewed by the principal investigator. Severe events and any unanticipated adverse events will additionally be reported to the institutional review board within 24 h of identification. Signs of persistent over-attachment, such as marked distress when separated from the doll, conflict with other residents, or interference with eating, sleep, hygiene, or clinical care, will trigger individualized review and adaptation. Safeguards to preserve dignity and autonomy include voluntary participation, proxy consent plus ongoing assent, non-deceptive introduction to families and staff, individualized stopping rules, private or respectful session settings, avoidance of infantilizing language, and documentation of adverse emotional or social reactions. Because this is a minimal-risk behavioral intervention with structured stopping rules and adverse-event review, no independent data monitoring committee is planned; this decision will be revisited if the adverse-event rate exceeds prior expectations.

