### Ethics and dissemination

The study was approved by the Institutional Review Board of the School of Medicine, Sias University (approval number LL20240509). The trial was prospectively registered at ClinicalTrials.gov (NCT06506487) on July 16, 2024. Written informed consent will be obtained from legally authorized representatives of participating residents, and assent will be sought from residents whenever appropriate. Separate written informed consent will be obtained from all qualitative interview participants.

The intervention will be introduced to legal representatives and family caregivers as an optional psychosocial activity designed to support comfort and engagement. Residents will be approached respectfully, and their verbal and non-verbal assent or dissent will be monitored continuously. Participation in doll therapy will be paused or stopped when residents show refusal, persistent distress, interpersonal conflict, or over-attachment that interferes with care or wellbeing. These procedures are intended to preserve dignity, autonomy, and safety while recognizing that proxy consent alone is insufficient for an ongoing psychosocial intervention among people living with dementia.

Any important protocol amendments will be communicated to participating sites and the ethics committee as appropriate. Findings will be disseminated through peer-reviewed publication, conference presentation, and a brief lay summary for participating nursing homes and family caregivers after study completion.

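### The safety and ethics sections state different actions on doll exposure for conflict with other residents and for over-attachment that interferes with care

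*Protocol article*

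**What the plan says.** Three places in the protocol article govern what happens to doll exposure.

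- **Safety monitoring and harms, paragraph on assent.** On any refusal or distress, "staff will stop the interaction for that occasion, remove or set aside the doll respectfully, provide reassurance, and record the event". Then: "Two consecutive sessions with refusal or significant distress will trigger an individualized review by the site clinician". Finally, "three consecutive refusals or any persistent doll-related distress will result in discontinuation of doll exposure for that participant". The same sentence keeps such residents in the intention-to-treat analysis. Conflict and over-attachment are listed earlier in the section as possible adverse responses, but this paragraph attaches no action to them.
- **Safety monitoring and harms, paragraph on adverse events.** "Signs of persistent over-attachment, such as marked distress when separated from the doll" opens the list of signs, which continues "conflict with other residents, or interference with eating, sleep, hygiene, or clinical care, will trigger individualized review and adaptation". The paragraph then lists "individualized stopping rules" among its safeguards. It closes by calling the stopping rules structured and giving them as part of the reason why no independent data monitoring committee is planned.
- **Ethics and dissemination.** Participation in doll therapy will be "paused or stopped when residents show refusal, persistent distress, interpersonal conflict, or over-attachment that interferes with care or wellbeing".

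**The concern.** Over-attachment and conflict over the doll are among the specific risks the protocol itself names. For these, a home that follows the safety section would review and adapt; a home that follows the ethics section would pause or stop. Both sections use the language of obligation, and neither refers to the other or says which prevails.

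Two things are at stake. First, the stopping rules support the decision to have no data monitoring committee. That support is weaker where the text gives two answers, and where the same paragraph calls the rules both individualized and structured. Second, the Outcomes section weights conclusions first toward feasibility, acceptability, fidelity, safety and implementation. Counts of discontinuation and records of continued doll use feed those results. If homes apply different rules to the same event, the counts would partly reflect which section each home followed.

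**Working it through.** No arithmetic applies. The check sets trigger against action across the three places.

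| Trigger | Safety section, assent paragraph | Safety section, adverse-event paragraph | Ethics section | Result |
|---|---|---|---|---|
| Refusal | Stop for the occasion; clinician review after two consecutive sessions; discontinue after three consecutive refusals | not addressed | pause or stop | Compatible: the ethics wording can summarize the graded steps |
| Over-attachment interfering with care | no action stated | review and adaptation | pause or stop | Two different actions |
| Conflict with other residents | no action stated | review and adaptation (as a sign of over-attachment) | pause or stop | Two different actions |
| Marked separation distress that persists | discontinue, if it counts as persistent doll-related distress | review and adaptation | pause or stop, if it counts as persistent distress or interferes with care or wellbeing | Possible three-way overlap, depending on the reading |
| Persistent distress in general | discontinue | no action on exposure stated | pause or stop | Discontinuation required in one place, a pause also allowed in the other |

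Reasoning through the rows:

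1. **Over-attachment interfering with care, and conflict.** The triggers in the adverse-event paragraph and the ethics section overlap directly. One action is review and adaptation; the other is a pause or stop. Adaptation could be understood to include a pause, but the text does not say so. This is the firm part of the finding.
2. **Separation distress.** The adverse-event paragraph treats it as a sign of over-attachment. The assent paragraph requires that "any persistent doll-related distress will result in discontinuation of doll exposure for that participant". Distress at being parted from the doll is doll-related in ordinary language, so persistent separation distress can fall under both. The assent paragraph, however, mainly describes dissent toward the doll, so this is a possible overlap and not a certain one.
3. **Persistent distress in general.** The safety section leaves no alternative to discontinuation; the ethics section also admits a pause.
4. **Analysis set.** Residents discontinued under the assent paragraph stay in the intention-to-treat analysis, so such a discontinuation does not change who is analyzed. The effect is on exposure and on the safety and feasibility counts.

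**The case against.** The best defense is that the ethics section is a summary. On that view its phrase spans everything from a temporary halt to the end point of a review, and a review under the safety section may itself end in a pause or stop. The safety section lists individualized stopping rules among its safeguards, and under Intervention and comparator families are told that participation can be halted whenever they wish. Deliverer training also covers recognition of over-attachment and escalation routes.

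Part of this stands. It reconciles the refusal row fully and shows that the safety section does not rule out a stop. It does not reconcile conflict or over-attachment that interferes with care. The ethics section says that a pause or stop will happen; the safety section says only that review and adaptation will.

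A reader might infer more than the text supports:

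- **That all three places clash over conflict and over-attachment.** The assent paragraph sets no action for either. A three-way overlap arises only through separation distress.
- **That exposure continues under the safety section.** That section is silent on exposure for these events; continuation would be inferred from silence.
- **That severe events are merely reported.** All adverse events are also reviewed by the principal investigator.
- **That the over-attachment review has no owner.** No role is named in that sentence, but this is detail that an article can leave to the full protocol.
- **That sites have no usable stopping rule.** The refusal steps are explicit and usable.

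**Conclusion.** The contradiction holds for two triggers: conflict with other residents, and over-attachment that interferes with care. For each, the safety section and the ethics section state different actions. Two lesser inconsistencies sit beside it: a possible double classification of persistent separation distress, and discontinuation versus pause-or-stop for persistent distress in general.

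Its size cannot be given as a number of residents, because the protocol gives no rate for these events. It reaches only intervention residents who have one of them. With three intervention homes, it is tempting to say that a divergent home would affect a third of exposed residents. That is only one home's share of the arm if homes are of equal size (1/3), not the share who would have such an event. Different handling by home is a foreseeable risk, not something the documents report.

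The conclusion assumes that both sections are meant as operating rules, as their wording indicates. The point does not threaten the trial's validity or its intention-to-treat analysis. It is worth correcting because it concerns resident safety, bears on the stated case for having no data monitoring committee, and costs little to resolve.

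**What to change.** Reconcile the two paragraphs of Safety monitoring and harms with Ethics and dissemination. Conflict with other residents, over-attachment that interferes with care, distress on separation, and persistent distress should each have one stated action on doll exposure. The sponsor and site clinicians should choose those actions, and all three intervention homes should apply them. State which rule governs when separation distress persists, so that one event does not fall under two. Report discontinuations by trigger and by home. No view is taken here on which action is right, and the refusal steps need no change on this account.

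Cost: a short protocol clarification and an update to the deliverer training. No additional residents or assessments are needed.

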### Outcomes

Outcomes are organized into a transparent hierarchy that distinguishes (i) the outcome registered in ClinicalTrials.gov, (ii) the outcome given interpretive primacy for proximal clinical response, (iii) secondary clinical outcomes, and (iv) exploratory contextual outcomes and process measures. This structure is intended to clarify what the trial can describe as feasibility-oriented, preliminary, or contextual evidence, and how each outcome should be weighted in interpretation given the exploratory pilot design. Overall conclusions will be weighted first toward feasibility, acceptability, fidelity, safety, and implementation signals; second toward NPI-12 as the validated proximal behavioral outcome; and only cautiously toward medication outcomes as indirect medication-stewardship signals.

### Registered primary outcome

The registered primary outcome (ClinicalTrials.gov NCT06506487) is class-specific mean daily medication dose for antipsychotics, anxiolytics, and antidepressants, measured at baseline, 6 weeks, and 12 weeks. Medication burden will be analyzed separately by drug class rather than as a single combined metric. These outcomes are clinically and policy-relevant because psychotropic exposure is common and potentially harmful in residential dementia care. However, they will not be interpreted as direct indicators of doll-therapy clinical effects or as the dominant basis for trial conclusions. They will instead be interpreted as indirect medication-stewardship signals because prescribing in nursing homes is clinician-led and shaped by physician practice, medication-review routines, family preferences, staffing capacity, acute illness, institutional policies, and medication-review opportunities.

Antipsychotic exposure will be standardized using chlorpromazine daily equivalents. Anxiolytic exposure will be standardized using diazepam daily equivalents for benzodiazepines and z-drugs; non-benzodiazepine, non-z-drug anxiolytics (for example, buspirone or hydroxyzine) will be quantified separately using the World Health Organization Defined Daily Dose (DDD) framework and described alongside benzodiazepine and z-drug equivalents. Antidepressant exposure will be quantified using the WHO DDD framework (22, 23). For each assessment point, the mean daily administered dose over the preceding 7 days will be calculated from medication administration records and physician orders, including scheduled and as-needed administrations where applicable. Participants not receiving a given medication class during the relevant assessment window will be assigned a dose of zero for that class. Because class-specific medication distributions may be sparse, skewed, or zero-inflated, each class will also be summarized descriptively using exposed counts and percentages, zero-exposure counts, medians and interquartile ranges, and initiation, discontinuation, and dose-reduction status where sample size permits. Psychotropic polypharmacy patterns will be reported descriptively at baseline, 6 weeks, and 12 weeks, including no exposure, monotherapy, two-class exposure, three-class exposure, and the most common class combinations. Any acute clinical events, hospital transfers, or documented medication reviews during the assessment window will be recorded where available to support cautious interpretation.

### Main proximal clinical outcome for interpretation

The main proximal clinical outcome for interpretation is the total Neuropsychiatric Inventory-12 (NPI-12) score, measured at baseline, 6 weeks, and 12 weeks, with between-group change at 6 and 12 weeks treated as the principal proximal clinical signal. The NPI-12 is a caregiver-rated instrument covering 12 neuropsychiatric domains (3). The NPI-12 was selected as the most direct, validated, behaviorally proximal measure of intervention response available in this trial. This terminology does not change the registered primary outcome; it clarifies how medication-related and behavioral outcomes will be weighted in interpretation.

### Secondary clinical outcomes

Activities of daily living will be measured using the modified Barthel Index (Chinese-language version commonly used in domestic long-term care research) scored from 0 to 100, with higher scores indicating greater independence (24, 25). Cognitive enhancer use will be examined as a secondary medication outcome and standardized using donepezil daily equivalents (26). Both outcomes will be assessed at baseline, 6 weeks, and 12 weeks.

### Exploratory contextual outcomes and process measures

Traditional Chinese medicine (TCM) use will be documented as an exploratory contextual medication outcome using a structured study-specific score that captures formula complexity, daily dosage, frequency, and duration. The TCM score has not been externally validated and will not be used for strong inferential claims; it is included to describe a locally relevant care context and to support exploratory interpretation of concurrent treatment patterns.

The scoring framework for traditional Chinese medicine use is summarized in Table 2.

**Table 2 tab2:** Study-specific exploratory scoring framework for traditional Chinese medicine use.

Scale	Scale description	Points
Complexity of formula	Based on the number of different herbs in the formula.	1 point: 1–5 herbs 2 points: 6–10 herbs 3 points: 11–15 herbs 4 points: >15 herbs
Dosage of formula	Based on the total daily dosage of the TCM formulation.	1 point: <=10 grams/day 2 points: 11–20 grams/day 3 points: >20 grams/day
Frequency of administration	Based on how often the formula is taken each day.	1 point: once daily 2 points: twice daily 3 points: three times or more daily
Duration of treatment	Based on the length of time the treatment is prescribed.	1 point: <1 month 2 points: 1–3 months 3 points: >3 months

This scoring framework was developed for the present study and has not been externally validated. It will be used as an exploratory contextual descriptor of concurrent traditional Chinese medicine use and not for strong inferential claims.

Structured engagement with the doll will be documented in the intervention arm as a process and exploratory outcome. Engagement indicators will include attendance at planned sessions, session duration, session format (individual or small group), physical interaction with the doll, verbal interaction, caregiving behaviors, positive affect, refusal, distress, interruption, and continued spontaneous use during routine care. Engagement data will be summarized descriptively and used to contextualize variability in NPI-12, Barthel Index, and medication-related outcomes.

### Participant- and cluster-level covariates

Participant-level variables will include age, sex, educational level, marital status, parental status, dementia type, dementia severity category, years since diagnosis, length of stay in the nursing home, comorbidity burden, baseline medication exposure, social interaction level, weekly participation in other therapeutic activities, and attachment-related or caregiving-history indicators (for example, prior parenthood, prior caregiving role, or doll or pet experience) where these are available from caregiver report or facility records. Cluster-level descriptors will include facility size, staffing pattern, dementia-care intensity, usual recreational activities, medication-review routines, and relevant co-interventions where available.

### Qualitative component

Phase II will use descriptive semi-structured interviews with staff members and family caregivers from intervention homes. Participants will be purposively sampled after sufficient exposure to the intervention to capture variation in professional role, facility, relationship to the resident, observed resident response, family perspective, and favorable, neutral, or unfavorable experiences. The anticipated sample is approximately 12–18 staff members and 6–12 family caregivers, with final recruitment guided by information power: sampling will continue until the data provide sufficient depth and variation to address the implementation, acceptability, and ethical questions of the study (27). Interview topics will include first impressions of doll therapy, observed resident responses, perceived benefits and harms, neutral or absent responses, refusal or distress, implementation challenges, training needs, cultural fit, ethical concerns, family communication, dignity and autonomy, and alternative explanations such as staff attention, structured interaction, or wider care-context changes.

Interviews will be conducted one-to-one in Chinese, audio-recorded with permission, transcribed verbatim, anonymized, and analyzed using Braun and Clarke’s reflexive thematic analysis framework (28). Coding will proceed iteratively. At least two members of the research team will review an initial subset of transcripts to discuss code definitions, emerging themes, and differences in interpretation. The coding framework will then be refined through team discussion and applied to subsequent transcripts, with active attention to negative and disconfirming cases, including accounts of refusal, distress, lack of benefit, family concern, staff burden, or explanations that attribute observed changes to attention or routine care rather than to the doll. Reflexive notes, coding decisions, and an audit trail will be maintained to support transparency and trustworthiness; the research team’s professional backgrounds, prior experience of dementia care, and assumptions about doll therapy will be documented at the outset and revisited as analysis proceeds, in line with reflexive qualitative practice. Reporting will follow the Consolidated Criteria for Reporting Qualitative Research (29). Because interviews are limited to intervention homes, the qualitative findings may be vulnerable to positivity bias and cannot provide a direct comparison with control-site staff experiences; this limitation will be stated explicitly in reporting.

### Sample size

No previous doll-therapy study in this setting has provided directly usable estimates for a cluster-level sample size calculation based on daily medication dose as the primary outcome. The target sample size was therefore derived pragmatically as a feasibility and planning target rather than as a definitive power calculation. The earlier participant-level G*Power calculation is retained only as a contextual planning anchor: using G*Power 3.1 (*F* tests, ANCOVA: fixed effects, main effects, and interactions; number of groups = 2; number of covariates = 1; numerator degrees of freedom = 1), assuming a medium effect size (Cohen’s *f* = 0.25), alpha = 0.05, and power = 0.80, 128 participants would be required for an individually randomized analysis of covariance including the baseline value of the outcome as a covariate. This calculation does not represent cluster-level power for the present design. Allowing for approximately 10% attrition due to acute deterioration, hospital admission, withdrawal, or death, the participant-level recruitment target was set at 142 to support feasibility estimation and preliminary signal detection.

Because the trial uses cluster randomization, the design effect was considered using the standard formula 1 + (*m* − 1) × ICC, where m is the average cluster size. With 142 participants across six nursing homes, the average cluster size is approximately 23.7. Directly comparable intracluster correlation coefficient (ICC) estimates for psychotropic medication-dose outcomes in Chinese dementia nursing homes are not available in the published literature, and empirical ICC values in long-term care vary substantially across outcomes, populations, and care settings (30–32). Sample size in cluster trials is also known to be highly sensitive to small differences in the assumed ICC, so any single value can only be treated as a planning assumption rather than as definitive (30). The most directly relevant published precedent is a UK cluster randomized trial of enhanced psychosocial care on antipsychotic use in nursing home residents with severe dementia, which used an ICC of 0.05 (33). Reported ICCs for related facility-level outcomes in older adults and healthcare cluster trials span approximately 0.005 to 0.10 depending on the outcome domain (31, 32).

To make this uncertainty transparent, we describe design effects and effective sample sizes across plausible ICC values rather than relying on a single point estimate. Under a low ICC of 0.005, the design effect is approximately 1.11 and the effective sample size is approximately 128. Under a moderate ICC of 0.02, the design effect is approximately 1.45 and the effective sample size is approximately 98. Under an ICC of 0.05, consistent with the most directly comparable nursing-home antipsychotic trial (33), the design effect is approximately 2.14 and the effective sample size is approximately 66. Under an ICC of 0.10, the design effect rises to approximately 3.27 and the effective sample size falls to approximately 43. These figures are descriptive sensitivity scenarios rather than formal power claims. They make explicit that the trial is unlikely to detect small or modest effects with confidence at any plausible ICC and reinforce the pilot and feasibility interpretation of all between-group estimates.

Because NPI-12 has been designated as the main proximal clinical outcome for interpretation, the same sample size and ICC scenarios were used to provide a directional sense of what behavioral signal might be detectable. Assuming a between-group standardized difference of approximately 0.5 standard deviations on the total NPI-12 score (i.e., approximately 5–7 points if the population standard deviation is in the 10–15 range typical of nursing-home dementia samples), the design might provide a preliminary signal under low ICC assumptions but would remain underpowered and imprecise for smaller changes or for moderate to high ICC values. NPI-12 changes will therefore be interpreted using effect estimates, 95% confidence intervals, and consistency across descriptive and cluster-level sensitivity analyses rather than dichotomous hypothesis testing.

The small number of randomized clusters is itself an important design limitation. With only three nursing homes per arm, the study is vulnerable to baseline imbalance, imprecise cluster-level effect estimates, unstable model-based standard errors, and sensitivity to site-specific practices. The trial is therefore not intended to support definitive claims about clinical effects. Instead, it will estimate recruitment, retention, adherence, fidelity, safety, acceptability, preliminary effect sizes, confidence intervals, and contextual factors needed to design a future larger cluster randomized trial, potentially with a stepped-wedge design or an active attention-control condition. Sensitivity analyses will include cluster-level summaries and randomization-based checks to make clear what magnitude and direction of difference could plausibly be observed with this design.

